# Cost-Effectiveness of Transcranial Magnetic Stimulation and Virtual Reality-Based Cognitive Remediation for Depressive Symptoms among Cancer Patients: Protocol for a Three-Arm Randomized Controlled Trial

**DOI:** 10.2174/0117450179376750250925051532

**Published:** 2026-03-24

**Keywords:** Depression, Cognitive functions, Quality of life, Cancer, Virtual reality, Repetitive transcranial magnetic stimulation

## Abstract

**Introduction:**

This paper presents a research protocol of a randomized controlled trial aimed to evaluate the feasibility and the cost-effectiveness of non-pharmacological interventions for depressive symptoms, quality of life, depression-related conditions, and cognitive function among patients with cancer. Specifically, repetitive transcranial magnetic stimulation (rTMS) and virtual reality-based cognitive remediation (VR-COG) will be analyzed, alongside standard treatment as usual (TAU), in comparison to TAU alone.

**Methods:**

100 participants will be enrolled: 60 from the Health Trust of Ferrara randomized 1:1:1 to (a) TAU, (b) rTMS + TAU, and (c) VR-COG + TAU, and 40 from the University Hospital of Cagliari randomized 1:1 to (a) TAU and (b) VR-COG + TAU. The inclusion criteria will be as follows: patients aged 18 years and older, both sexes, a diagnosis of oncological disease within the last 5 years in a non-advanced stage, a diagnosis of major depressive disorder according to DSM-5 criteria, and a score of≥14 on the 17-item Hamilton Rating Scale for Depression (HAM-D-17). The VR-COG program will include a series of exercises in virtual sailing scenarios using the software CEREBRUM. The rTMS program will be delivered at 50% of the resting motor threshold. Personalized targets created for each individual will be located at various cortical depths. TAU will include psychiatric visits and psychological counseling. All the interventions will last 3 months, with pre-post evaluation for outcomes of interest and 3-6 months of follow-up.

**Results:**

The results of the trial will be published in international peer-reviewed journals and will be disseminated at international meetings and congresses.

**Discussion:**

The results of this study will be useful for obtaining knowledge for clinical practice regarding the feasibility and cost-effectiveness of innovative therapeutic approaches aimed at treating depression in individuals suffering from oncological pathologies.

**Conclusion:**

The monitoring of the program's cost-effectiveness, encompassing both the screening and intervention phases, will enable policymakers to inform the implementation of this evidence in routine clinical practice.

**Clinical Trial Registration Number:**

The study has been registered on the ClinicalTrials.gov website with ID no. NCT06589544.

## INTRODUCTION

1

Approximately one in four persons with cancer expresses symptoms of depression [1]. Individuals with cancer and depression are at high risk for severe disability, challenges in returning to work, high risk of suicide, lack of adherence to treatment, poorer prognosis, and decreased survival [2]. Additionally, depression increases the number of visits, hospital admissions, and medical costs [3]. Depression is specifically linked to cognitive deficits in memory, learning, attention, and concentration [4], as well as sleep disturbances, disability, difficulties at work, and suicide risk, all of which worsen the prognosis and increase the risk of relapses or chronicity [2, 5].

Among people with cancer, depression is particularly not recognized or treated. Only 10% of patients receive mental health care. In this sense, primary prevention is practically absent [6] due to the lack of effective screening tools and the poor structure of specialized medical education courses in the Italian and international contexts [7]. Developing personalized screening tools could improve the identification of high-risk patients and their enrolment in specialist treatment pathways at the second or third level [7, 8]. Despite its significant impact on individuals and healthcare systems, substantial gaps remain in the clinical and rehabilitative management of depression among people with cancer. There are no specific guidelines for psychotropic drug usage, and the efficacy of antidepressants is uncertain despite their frequent use [9].

Among non-pharmacological treatments, physical activity is recognized for its preventive and rehabilitative efficacy in addressing mental health complications, particularly concerning depressive and anxiety symptoms [10].

Even if emerging therapeutic strategies, like repetitive transcranial magnetic stimulation (rTMS) and cognitive virtual reality (VR)-based cognitive remediation programs, show promising findings, their cost-effectiveness is understudied [3]. rTMS is already used for the treatment and relapse prevention of depression, both as mono-therapy and as an add-on treatment to antidepressant pharmacotherapy, and it appears effective in improving cognitive performance [11]. However, it has not yet been applied to treat depressive disorders in oncology patients. VR-based cognitive remediation interventions (VR-COG) are designed to improve cognitive functioning, a central feature of depression, even in oncological conditions. VR-COG enhances learning and skill acquisition with better ecological efficiency than traditional cognitive remediation programs [12, 13]. VR approaches are well-received by people with cancer and show promise in reducing anxiety and depressive symptoms [14, 15]. In particular, a VR-COG program has been shown to be feasible and effective not only for improving cognitive functions, but also for reducing depressive and anxiety symptoms, thus enhancing quality of life and improving alexithymia and the regulation of biological and social rhythms in individuals with bipolar disorder [16-22].

This trial aims to evaluate the preliminary effective-ness of highly specialized, nonpharmacological interventions for depressive symptoms among people with cancer and their feasibility according to dropout rates and the proportion of recruited participants among those considered eligible (primary outcomes). The secondary outcomes include the preliminary effectiveness of the interventions in improving quality of life (QoL), addressing depression-related conditions, and enhancing cognitive functions. Specifically, compared to treatment as usual (TAU), rTMS and VR-COG will be tested alongside standard TAU. This trial also aims to evaluate and verify the cost-effectiveness of these treatments (tertiary outcome). This study has been designed as a pragmatic randomized controlled trial, aiming to assess the effectiveness and cost-effectiveness of two non-pharmacological interventions as they would be implemented in real-world oncology settings. We have prioritized external validity and clinical applicability over mechanistic control, using TAU as a comparator to reflect standard care conditions [23].

## MATERIALS AND METHODS

2

### Study Design

2.1

The study will involve a randomized controlled trial (RCT) among persons with oncological diseases and mild-moderate depression. The study will include a longi-tudinal, three-arm design with participants assigned by randomization to either an active interventional protocol based on repetitive transcranial magnetic stimulation (rTMS) + treatment as usual (TAU) or virtual reality-based cognitive remediation (VR-COG) + TAU, and to a control setting, treatment as usual (TAU). The main outcomes are expected to show the superiority of each experimental intervention (rTMS + TAU or VR-COG +TAU) over the control condition (TAU). Participants will be randomized, independently, to parallel intervention groups in each of the two units [unit 1, Health Trust of Ferrara (UniFE), with 1:1:1 randomization to (a) TAU, (b) rTMS + TAU, and (c) VR-COG + TAU; unit 2, University Hospital of Cagliari (UniCA), with 1:1 randomization to (a) TAU and (b) VR-COG + TAU] with the stratification for the unit of the recruitment.

The timeline of the different study phases and the protocol flow diagram are presented in Figs. (**1** and **2**), respectively.

### Participants and Recruitment

2.2

The target population for this study will be subjects with oncological diseases and moderate depression. Inclusion criteria will be as follows: patients aged 18 years and older of both genders; diagnosis of oncological disease in the last 5 years; depression without psychotic symptoms according to Hamilton Rating Scale for Depression (HAM-D-17) score ≥14; and oncological disease in a non-advanced stage (Karnofsky performance status > 80).

Exclusion criteria will comprise current or prior hospitalization in the next 6 months, planned surgery in the next 6 months, suicidal ideation, substance use, history of significant head trauma, neurological disorders, intellectual deficits, recurrent seizures resulting from head trauma or conditions lowering seizure threshold, concurrent use of medications that increase the risk of epileptic seizures (*e.g.*, antipsychotics, tricyclics, theophylline), glaucoma, retinal detachment, or other serious vision impairments that may prevent the use of virtual reality technology and severe problems with autonomous ambulation.

According to the inclusion/exclusion criteria, recruitment will continue until the target sample size is reached, allowing for randomization and the conduct of interventions (Figs. **1** and **2**).

### Outcomes

2.3

The following outcome measures will be established for each participant based on clinical relevance, Cochrane Collaboration indications, and cost-effectiveness studies.

The primary outcomes will include depressive symptoms and the study’s feasibility indicators (acceptability, tolerability, side effects, or secondary effects due to the use of technological devices).

The secondary outcomes will comprise quality of life, cognitive functions (immediate memory, working memory, phonemic verbal fluency, delayed memory, psychomotor speed, executive function, selective attention), and other depression-related conditions (demoralization, embitter-ment reactions to negative life events, psychological distress, insomnia, social and biological rhythms dysregulation, disability level, and alexithymia).

The tertiary outcome will include the cost-effectiveness of the nonpharmacological interventions (VR-COG, rTMS) in addition to TAU compared to TAU alone.

### Evaluation Tools and Evaluation Timeline

2.4

To assess the primary outcomes, the tools and evaluation procedures that will be used are as follows:

Hamilton Depression Rating Scale, comprising 17 items (HAM-D-17) [24], is a clinician-administered tool widely used to assess the severity of depressive symptoms, which evaluates mood, guilt, suicide ideation, insomnia, and somatic symptoms over the preceding week. Each item is rated on a 3- or 5-point scale, with higher scores indicating greater depression severity. Its reliability and validity have been extensively established. The scale will be administered according to the following timeline: T0 (0 months-baseline), T1 (3 months-post-intervention), T2 (3 months after T1), and T3 (6 months after T1).Drop-out rates, the proportion of recruited participants among those considered eligible, and secondary or side effects due to virtual reality or repetitive transcranial stimulation will be the measures employed to assess the feasibility of the study. These will be estimated according to the following timeline: T0 (0 months-baseline), T1 (3 months-post-intervention), T2 (3 months after T1), and T3 (6 months after T1). Side and secondary effects will be assessed through the Simulator Sickness Questionnaire [25], a self-report questionnaire including 16 items that evaluate the frequency of unwanted effects due to virtual reality technologies, such as nausea, dizziness, headaches, eye strain, *etc.* The TMSens_Q questionnaire [26] will be used to evaluate various unintended sensations and adverse effects, ranging from mild side effects to serious adverse events related to the use of rTMS. The questionnaire will be administered according to the following timeline: T0 (0 months-baseline) and T1 (3 months-post-intervention). Figure **1** provides a summary of the timeline.

To assess the secondary outcomes, the following tools and evaluation procedures will be employed:

EuroQol (EQ)-5D is a self-report questionnaire to assess health-related quality of life [27]. It encompasses two parts: a descriptive one and a visual analogue scale (VAS). The descriptive part includes five dimensions, including mobility, self-care, usual activities, pain/
discomfort, and anxiety/depression, with each rated on a three-level (EQ-5D-3L) or five-level (EQ-5D-5L) scale, indicating no problems to extreme problems. The VAS records the respondent's self-rated health on a scale from 0 (worst health imaginable) to 100 (best health imaginable). It demonstrates good internal consistency and reliability, with Cronbach's alpha values ranging from 0.6 to 0.85, varying based on the population and clinical context.The SF-12 Health Survey [28] is a brief version of the widely used SF-36, designed to measure health-related quality of life. It consists of 12 items that cover physical and mental health domains. The SF-12 assesses the impact of health on daily functioning, pain, energy, emotional well-being, and role limitations due to physical or emotional problems. It demonstrates good internal consistency and reliability, with Cronbach's alpha values typically exceeding 0.80 for both physical and mental health domains.

Both of the above questionnaires will be administered according to the following timeline: T0 (0 months-baseline), T1 (3 months-post-intervention), T2 (3 months after T1), and T3 (6 months after T1).

Screen for Cognitive Impairment in Psychiatry (SCIP) [29] is a brief and validated neuropsychological tool designed to assess cognitive functioning in individuals with psychiatric disorders. It evaluates key cognitive domains, including verbal learning, working memory, processing speed, and executive functions, making it particularly useful in detecting cognitive impairments associated with conditions, such as schizophrenia, bipolar disorder, and major depressive disorder. The SCIP is time-efficient, typically requiring 10-15 minutes to administer, and has demonstrated high reliability, with Cronbach's alpha values ranging from 0.74 to 0.90, depending on the population and cognitive domain assessed. The scale will be administered according to the following timeline: T0 (0 months-baseline), T1 (3 months-post-intervention), T2 (3 months after T1), and T3 (6 months after T1).Trail Making Test [30] is a widely used neuropsychological assessment tool designed to evaluate cognitive flexibility, visual attention, and processing speed. It consists of two parts as follows: TMT-A, which requires participants to connect numbered circles sequentially, and TMT-B, which alternates between numbers and letters, assessing more complex executive functions, such as task-switching and set-shifting. Reliability studies have reported Cronbach's alpha values ranging from 0.70 to 0.89, depending on the sample and testing conditions. The questionnaire will be administered according to the following timeline: T0 (0 months-baseline), T1 (3 months-post-intervention), T2 (3 months after T1), and T3 (6 months after T1).Digit Span [31] is a neuropsychological test that evaluates working memory, attention, and immediate verbal memory. It consists of two components as follows: digit span forward, which evaluates simple attention and memory span by requiring participants to repeat a sequence of numbers in the same order, and digit span backward, which assesses working memory and cognitive flexibility by requiring participants to repeat the sequence in reverse order. Reliability studies have reported Cronbach's alpha values ranging from 0.70 to 0.90, indicating good internal consistency across different populations and testing contexts. The test will be administered according to the following timeline: T0 (0 months-baseline), T1 (3 months-post-intervention), T2 (3 months after T1), and T3 (6 months after T1).Stroop Test [32] is a widely used neuropsychological test that measures cognitive control, selective attention, and processing speed. It evaluates the ability to inhibit automatic responses and resolve cognitive interference by requiring participants to identify the ink color of a word that may denote a different color name (*e.g.*, the word “red” printed in blue ink). The test typically includes three conditions: “reading color names”, “naming colored blocks”, and “naming the ink color of incongruent color-word pairs”. The Stroop effect, reflected in the increased time or errors during the incongruent condition, provides insights into executive functioning and attentional control. Reliability studies have reported Cronbach's alpha values ranging from 0.72 to 0.91, depending on the test version and population studied. The test will be administered according to the following timeline: T0 (0 months-baseline), T1 (3 months-post-intervention), T2 (3 months after T1), and T3 (6 months after T1).Frontal Assessment Battery (FAB) [33] is a brief neuropsychological tool designed to evaluate executive functioning and frontal lobe cognitive abilities. It consists of six subtests assessing different aspects of executive function: conceptualization, mental flexibility, motor programming, sensitivity to interference, inhibitory control, and environmental autonomy. Studies have reported Cronbach's alpha values ranging from 0.78 to 0.90, indicating good internal consistency across various populations. The test will be administered according to the following timeline: T0 (0 months-baseline), T1 (3 months-post-intervention), T2 (3 months after T1), and T3 (6 months after T1).Rey's Word Test [34] is a neuropsychological assessment tool used to evaluate verbal memory and malingering by assessing an individual’s ability to recall and recognize words presented in a list format. The Cronbach’s alpha falls within a range of 0.70 to 0.85, depending on the specific population and administration conditions, indicating acceptable to good internal consistency. The test will be administered according to the following timeline: T0 (0 months-baseline), T1 (3 months-post-intervention), T2 (3 months after T1), and T3 (6 months after T1).Matrix test [35] is a cognitive assessment tool designed to evaluate non-verbal reasoning, abstract thinking, and problem-solving abilities. It typically involves identifying patterns or completing sequences in visual matrices. The reliability of the Matrix test, as indicated by Cronbach’s alpha, generally ranges from 0.80 to 0.90, reflecting good to excellent internal consistency. The test will be administered according to the following timeline: T0 (0 months-baseline), T1 (3 months-post-intervention), T2 (3 months after T1), and T3 (6 months after T1).Demoralization Scale (DS) [36] is a 24-item self-administered questionnaire with four subscales: discouragement, loss of meaning/purpose, dysphoria, and sense of failure. It measures feelings of helplessness, loss of meaning, and subjective incompetence, often associated with psychological distress in medical and psychiatric contexts. The questionnaire demonstrates high reliability, with Cronbach’s alpha typically ranging from 0.85 to 0.95, indicating excellent internal consistency across diverse populations. It will be administered according to the following timeline: T0 (0 months-baseline), T1 (3 months-post-intervention), T2 (3 months after T1), and T3 (6 months after T1).Post-traumatic Embitterment Disorder Self-rating Scale (PTED Scale) [37] is a 21-item tool designed to assess the symptoms of post-traumatic embitterment disorder (PTED), a condition that emerges following a significant, often unfair, negative life event. This disorder is characterized by persistent feelings of embitterment, resentment, and anger, which may lead to emotional and social difficulties. The Cronbach’s alpha coefficient indicates good internal consistency, ranging from 0.85 to 0.95. The scale will be administered according to the following timeline: T0 (0 months-baseline), T1 (3 months-post-intervention), T2 (3 months after T1), and T3 (6 months after T1).Brief Symptom Inventory (BSI) [38] is a widely used self-questionnaire designed to evaluate a range of psychological symptoms and distress. It consists of 53 items, which assess nine primary symptom dimensions, including anxiety, depression, and somatization, as well as a global severity index (GSI) that measures overall psychological distress. The internal consistency of the BSI is high, with Cronbach’s alpha values ranging from 0.70 to 0.90 across various subscales, indicating strong reliability in measuring psychological symptoms. The questionnaire will be administered according to the following timeline: T0 (0 months-baseline), T1 (3 months-post-intervention), T2 (3 months after T1), and T3 (6 months after T1).Insomnia Severity Index (ISI) [39] is a self-report questionnaire to assess the severity of insomnia symptoms. It consists of 7 items that evaluate the degree of difficulty with sleep initiation, sleep maintenance, early morning awakening, and the impact of these symptoms on daily functioning. The scale has demonstrated strong internal consistency, with Cronbach’s alpha values ranging from 0.74 to 0.90. The questionnaire will be administered according to the following timeline: T0 (0 months-baseline), T1 (3 months-post-intervention), T2 (3 months after T1), and T3 (6 months after T1).Biological Rhythms Interview for Assessment in Neuropsychiatry (BRIAN) [40] is a scale consisting of 18 items to assess four areas of circadian rhythm difficulties: sleep, activity, social rhythms, and eating patterns. The scale demonstrates good internal consistency, with Cronbach’s alpha value ranging from 0.80 to 0.90, indicating its reliability as an assessment tool for biological rhythm dysregulation. The questionnaire will be administered according to the following timeline: T0 (0 months-baseline), T1 (3 months-post-intervention), T2 (3 months after T1), and T3 (6 months after T1).Activities of Daily Living (ADL) [41] is a questionnaire that evaluates the ability to perform basic self-care tasks and daily activities to estimate the functional status and disability. Its internal consistency is strong, with Cronbach’s alpha value ranging from 0.70 to 0.90. The questionnaire will be administered according to the following timeline: T0 (0 months-baseline), T1 (3 months-post-intervention), T2 (3 months after T1), and T3 (6 months after T1).Psychosocial Adjustment to Illness (PAIS) [42] is a self-report instrument to evaluate the psychosocial impact of illness on an individual’s life. It examines seven domains, including social relationships, emotional well-being, work and leisure activities, and family dynamics, in response to chronic illness or medical conditions. It has demonstrated good internal consistency, with Cronbach’s alpha value ranging from 0.80 to 0.95, reflecting its reliability in capturing the psychological and social adjustments with illness. The questionnaire will be administered according to the following timeline: T0 (0 months-baseline), T1 (3 months-post-intervention), T2 (3 months after T1), and T3 (6 months after T1).

Toronto Alexithymia Scale 20-item (TAS-20) [43] is a self-report questionnaire designed to assess the degree of alexithymia. It consists of 20 items that measure three key dimensions of alexithymia: difficulty identifying feelings, difficulty describing feelings, and externally oriented thinking. The instrument demonstrates strong internal consistency, with Cronbach’s alpha ranging from 0.80 to 0.90. The questionnaire will be administered according to the following timeline: T0 (0 months-baseline), T1 (3 months-post-intervention), T2 (3 months after T1), and T3 (6 months after T1). A summary of the timeline is provided in Fig. (**1**).

The tertiary outcome will be measured as cost-effectiveness [3] of the nonpharmacological treatments (VR-COG and rTMS), and it will be computed as the ratio of total costs divided by the mean improvements of quality of life across interventions (TAU, TAU+rTMS, TAU+VRCOG). Total costs will include the costs of the healthcare consultations (visits in the TAU condition), psychotropic drugs, equipment, and staff. Total costs will be computed as the sum of the costs of each intervention, divided by the number of patients. Quality of life improvements will be computed as the difference between the baseline (T0) and the endpoint (T3) quality of life. A summary of the timeline is provided in Fig. (**1**).

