#### Experimental 1: Virtual Reality-based Cognitive Remediation (VR-COG) + Treatment as Usual (TAU)

2.9.2

 The "VR-COG" experimental protocol integrates sailing virtual environments within the CEREBRUM software platform (Idego-Promind, srl, Rome, Italy). It is based on the virtual reality software CEREBRUM (Idego-Promind, srl, Rome, Italy). The virtual scenarios dedicated to the sport of sailing offer four cognitive training exercises, each with three progressively challenging levels of difficulty, designed to train different cognitive functions (*i.e.*, executive functions, motor ability, language). The different degrees of difficulty are designed to adapt to the user's functional diagnosis. Each session, after an initial part of welcome, psychoeducation, and orientation to the instrument, involves alternating virtual reality exercises, positive and corrective feedback, and suggestions of practical homework that the individual should try to do during the day [16-22]. The frequency is 24 sessions, 2 times a week, for 12 consecutive weeks. The duration of each session is 50 minutes.

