#### Experimental 2: Repetitive Transcranial Magnetic Stimulation (rTMS) + Treatment as Usual (TAU)

2.9.3

The rTMS group will receive active rTMS using the MagVenture MagPro X100 System (MagVenture A/S, Denmark) equipped with a MagVenture Cool-B65 A/P double-faced coil and a neuronavigation system (Localite GmbH, Sankt Augustin, Germany). Active rTMS stimulation will be delivered at 50% of the resting motor threshold (rMT). Personalized targets created for each individual will be located at various cortical depths. For safety reasons, the stimulation intensity will never exceed 120% of the rTMS [44, 45]. The frequency will be 24 sessions, 2 times a week, for 12 consecutive weeks of rTMS with the intermittent theta burst stimulation (iTBS) protocol on the left dorsolateral prefrontal cortex (DLPFC). The daily sessions will consist of 3 consecutive sessions of 600 pulses, with each session comprising triplets of pulses at a frequency of 50 Hz, repeated every 200 ms (5 Hz bursts).

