#### Adverse Event Reporting

2.9.6

The clinicians in charge of TAU at each appointment will collect, report, evaluate, and manage adverse events or other unexpected effects of the interventions being studied or related to the trial's implementation. Each adverse event will be reported, including details about the type of adverse event, its beginning and end, severity, whether or not it could have been expected, its outcome, and whether or not it was related to the study.

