### Risk and Benefits

3.1

The use of immersive virtual reality (VR) may be associated with mild and transient side effects, including dizziness, nausea, headaches, visual fatigue, impaired limb coordination, diminished postural stability, a decreased sense of presence, and potentially inappropriate reactions to real-world environments. The side effects of rTMS are also mild and transient, and include headache, discomfort at the scalp stimulation site, tingling sensations or muscle twitching, and light-headedness. Nonetheless, significant adverse effects are not expected, as rTMS and VR are considered safe and well-tolerated procedures, with an extremely low risk of side effects [16, 57-60].

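### The side-effect questionnaires, part of the primary outcome, have no time point during the 24 device sessions, so effects the plan calls transient are likely to be under-recorded

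*Protocol article*

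**What the plan says.** **Outcome.** Section 2.3 of the protocol article places among the primary outcomes the study's "feasibility indicators (acceptability, tolerability, side effects, or secondary effects due to the use of technological devices".

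**Instruments and timing.** Section 2.4 names the Simulator Sickness Questionnaire for VR, said to "evaluate the frequency of unwanted effects due to virtual reality technologies", and TMSens_Q for rTMS. It gives two timelines. For the feasibility measures, including side effects: "These will be estimated according to the following timeline: T0 (0 months-baseline), T1 (3 months-post-intervention), T2 (3 months after T1", and then T3, six months after T1. Directly after TMSens_Q: "The questionnaire will be administered according to the following timeline: T0 (0 months-baseline) and T1 (3 months-post-intervention". No recall period is given for either form.

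**Exposure.** Section 2.9.2, for VR-COG: "The frequency is 24 sessions, 2 times a week, for 12 consecutive weeks". Section 2.9.3, for rTMS: "The frequency will be 24 sessions, 2 times a week, for 12 consecutive weeks of rTMS". Section 2.6 puts randomization after the baseline assessment.

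**Expected effects.** Section 3.1 calls the effects of immersive VR mild and transient, and continues: "The side effects of rTMS are also mild and transient".

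**Other capture.** Section 2.9.6: "The clinicians in charge of TAU at each appointment will collect, report, evaluate, and manage adverse events", with type, start and end, severity and relatedness. Section 2.9.5 plans outcome data from participants who withdraw early. Section 2.11 imputes missing data by LOCF.

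**The concern.** An effect expected to be short-lived is best recorded close to the exposure that causes it. Here the exposure is spread over 12 weeks, and the forms named to measure it are scheduled before the first session and after the course. A T0 reading cannot contain a device effect. Readings three and six months after T1, if taken, are far from any session. One reading per patient is left to inform a primary outcome.

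This matters because section 4 presents the study as a pilot meant to guide later trials, which makes tolerability one of its main products. If nausea, headache or scalp discomfort came and went during the course, a single reading at T1 could understate how often they occurred and how bad they were. Such data cannot be recovered afterwards. The two timelines also leave sites unsure which forms are due at T2 and T3.

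**Working it through.** **Step 1: sessions between T0 and T1.** Sections 2.9.2 and 2.9.3 give 2 sessions a week for 12 weeks: 2 × 12 = 24. This reproduces the stated figure for both devices.

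**Step 2: the timelines against the exposure window.**

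| Time point | Position | In T0–T3 timeline | In T0/T1 timeline |
|---|---|---|---|
| T0 | before randomization and exposure | yes | yes |
| Sessions 1 to 24 | weeks 1 to 12 | none | none |
| T1 | post-intervention, 3 months | yes | yes |
| T2, T3 | 3 and 6 months after T1 | yes | no |

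The timelines differ only in visits after treatment. Which one governs does not change the number of on-treatment readings, which is zero. The T0/T1 sentence is in the singular and follows TMSens_Q, so applying it to the Simulator Sickness Questionnaire is a reading; if that form follows T0–T3 instead, it still has no on-treatment point.

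**Step 3: worst-case coverage.** Planned arms from the abstract: rTMS 60/3 = 20; VR-COG 60/3 + 40/2 = 40. Device sessions: (20 + 40) × 24 = 1,440. If T1 fell on the day of the last session and reflected only that session, there would be at most 60 readings: 60/1,440 = 1/24 = 4.2%. If T1 fell on a later day, no session would be directly followed by a form.

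**Step 4: what that could mean per patient (illustration).** The article gives no per-session risk. Assume a risk p between 2% and 20%, independent across sessions. The chance of at least one episode in 24 sessions is 1 − (1 − p)^24. If T1 reflects only the last session, the chance of seeing one there is p.

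| Assumed p | At least one episode in 24 | Visible at T1, worst case |
|---|---|---|
| 2% | 38% | 2% |
| 5% | 71% | 5% |
| 10% | 92% | 10% |
| 20% | over 99% | 20% |

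At p = 5% this is about 14 of 20 against 1 of 20 (rTMS), and about 28 of 40 against 2 of 40 (VR-COG). If patients recall the whole three months at T1, the gap shrinks.

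**Step 5: the other route.** TAU counselling is described as bi-monthly over 12 weeks: about 6 contacts if twice a month, 1 to 2 if every two months. Adverse events are collected at these appointments, with start and end, so some on-treatment capture exists. The appointments are not tied to device sessions, and section 2.4 does not name this collection as a measure of the side-effect outcome.

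**Step 6: early stoppers.** Section 2.9.5 offers remote evaluations or new check-ups at 3, 6 and 9 months. For someone who stops early, these may fall well after the last session. If no reading is obtained, and if LOCF is applied to these scales, the value carried forward is the T0 score, taken before exposure.

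**The case against.** The strongest opposing case is that the plan does not rely on the questionnaires alone. Adverse events are collected at every TAU appointment, and recording start and end is how a resolved event gets documented. Section 2.9.7 adds monthly meetings that monitor safety. Section 2.9.5 commits to outcome data after early withdrawal. Drop-out is itself a primary feasibility measure, so intolerance that makes patients stop will show there. The Simulator Sickness Questionnaire is said to assess frequency, which is compatible with looking back over the course. The article is condensed, and Figure 1, to which it refers for the timeline, is not shown. The sample size and efficacy boundaries concern remission and do not use side-effect scores.

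Much of this stands, and it rules out several stronger inferences:

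- A reader might infer that side effects are sampled only before and after the course. That is true of the questionnaires, not of adverse events.
- A reader might infer that a transient effect cannot be seen at T1. Without a stated recall window, that does not follow.
- A reader might infer that an early stopper has only a pre-exposure form. Section 2.9.5 may supply a later one.
- A reader might infer that session staff are excluded from reporting. No section says who delivers the sessions.

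The mismatch remains. The article does state a schedule for these forms, so this is not detail left to a fuller document. Drop-out gives a count without symptom or severity and misses patients who endure side effects and stay. Adverse-event data are not linked to the outcome.

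**Conclusion.** The point holds in limited form. The questionnaires that measure a primary outcome have no time point during the 24 sessions under either stated timeline, the timelines conflict, and the plan itself expects the effects to be transient. Under-recording is therefore likely, and tolerability may look better than it is.

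The size is not fixed by the article. Coverage of 1 in 24 sessions is a worst case; it assumes that T1 reflects the last session only. The per-patient figures also rest on an assumed, independent per-session risk. Recall at T1 and adverse-event collection would narrow the gap by an unknown amount. It would go too far to conclude that the trial will report good tolerability because of when it measured: the direction is plausible, but the effect on the overall feasibility conclusion is not shown. The LOCF problem arises only if a post-exposure reading is missing and LOCF is applied to these scales.

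Severity: moderate. It is worth acting on because the remedy is cheap and on-treatment data cannot be collected later.

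**What to change.** 1. Reconcile the two timelines in section 2.4, stating for each form which visits apply and the recall period.
2. Give the Simulator Sickness Questionnaire (VR-COG) and TMSens_Q (rTMS) right after a few fixed sessions already scheduled, for example one early, one in the middle and the last.
3. For anyone who stops, give the form as soon as possible after the last attended session.
4. Have someone other than the blinded evaluator collect the forms, since a device-specific form reveals the arm.
5. Report the proportion with any on-treatment effect and the worst on-treatment score. Do not carry T0 forward for these scales.
6. State whether adverse events collected under section 2.9.6 count toward the side-effect outcome.

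The cost is a schedule amendment and a few minutes of self-report at visits that already take place. Reported side-effect rates will probably be higher.
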